### Monitoring and Harms

Monitoring of the study will be done by the Erasmus MC and will take place once a year. During the monitoring, the following will be monitored: (1) study documents and agreements; (2) patient inflow, consent, compliance, and source document verification; (3) patient safety; (4) the investigational intervention (VR); and (5) the study procedures.

The risk associated with the VR intervention is negligible and the burden should be considered minimal.

### Protocol Amendments

Modification to the protocol, which may impact on the conduct of the study and potential benefit of the patient or may affect patient safety, will require a formal amendment to the medical ethical committee of the Erasmus MC.

### Confidentiality

The handling of patient data will comply with the General Data Protection Regulation. All study data will be handled confidentially and coded with a unique study number. Only the research team involved in the study will be able to identify participants and have access to the data.

### Statistical Analysis

#### Overview

The primary analysis will be conducted using an intention-to-treat basis. All patients recruited into the study will be included in this analysis. Patients will be analyzed within the group to which they were randomized, irrespective of what care they received. Regarding missing data, first, it will be analyzed if missing data/loss to follow-up reflects information bias or selection bias. Second, multiple imputation will be used to control for bias due to missing data.

#### Primary Study Parameter(s)

To test the efficacy of the VR intervention, we will compare the VR group to the CAU group with an ANCOVA. The primary outcome variable is the child’s situational anxiety during MRI scan (T3; VAS child, continuous score), corrected for age, sex, baseline anxiety, and CBCL scores as well as type of MRI. In case of nonnormality, we will perform a Mann-Whitney *U* test.

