### Patient Recruitment and Procedure

For the prospective recruitment of patients, in concert with the radiologist, the planned MRIs will be scanned a month ahead for eligible patients. They will be informed about the study by mail or phone. If needed, they will be reminded by phone in the following weeks. Besides the reminder, this will help to overcome doubts, because the staff can answer questions or motivate the patients to participate.

All participants will receive an invitation, information folders, and an informed consent form. Participation is not obligatory, and all data will be anonymized. Parents of all the patients will be asked to sign informed consent. Children aged 12-14 years will also be asked to provide informed assent themselves. Patients aged younger than 12 years will give their verbal permission.

After receiving signed informed consent, the participants will be stratified by the type of MRI scan (head or body scan). Then, they will be randomly assigned to the VR group (n=64) or the CAU group (n=64).

The children assigned to the VR group will receive Google cardboard–like VR glasses and instructions on how to download the VR app on their phone and use the VR intervention at home. They will receive a log-in code to use the smartphone VR app. Adherence will be promoted by giving the participants detailed information about the purpose of the study and how to use the VR preparation app and explaining how they can get help from the contact support staff if there are difficulties with the app or VR glasses.

The allocation sequence was executed by a researcher who is not involved in the assessment phase. The psychologist who assesses the child’s anxiety state is blinded to the group assignment. This way, blinding for the treatment allocation will be guaranteed. Parents and children in both groups will be asked not to discuss their treatment allocation with the nurse, radiologist, or research psychologist.

Questionnaires will be assessed at the following time points: (1) T1, the weeks before the MRI scan (at home); (2) T2, the day of the MRI scan, before the procedure will start (in the waiting room); and (3) T3, right after the MRI scan (in the waiting room). The T3 questionnaires will retrospectively assess the child’s experience during the MRI scan. In this way, we can measure the anxiety during the MRI scan without the interruption of the procedure.

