#### Child Anxiety

The anxiety level of participants is measured before and after the MRI scan (T2 and T3) with the STAI-C, a questionnaire where parents and children evaluate statements on a scale from 0 (not at all) to 4 (completely true). The STAI-C is a widely used and validated self-report instrument for measuring state and trait anxiety [24]. The STAI-C has a good-to-excellent interobserver and intraobserver reliability and was validated in Dutch [25]. The VAS will be used to assess the child’s anxiety level by the child himself, the parents, and the medical staff. The VAS shows 6 faces in order from not scared at all (most left face) to extremely scared (most right face; see Figure 3) [26]. The participants select the expression that fits their feeling before and after the MRI scan (T2 and T3). Because of the nonverbal character and the simplicity, this instrument offers a quick and reliable assessment that can be used in different settings [27,28]. The VAS is a widely used and studied instrument, has been shown to have a good reliability and validity, and is validated in Dutch [29]. The medical staff who accompanied the child were instructed to observe the anxiety of the child before the procedure in the MRI room and during the MRI scan (T2 and T3) by using the VAS [30].

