#### Parental Anxiety

Parents/guardians rate their own feelings of anxiety with the STAI at T2 and T3. This self-report instrument contains 2 separate scales for trait and anxiety, combined into 40 items that the respondent rates as not at all (0), somewhat (1), moderately (2), or very much (3). Earlier studies identified the STAI as a validated and reliable instrument to measure the anxiety state of the parents, and it is validated in Dutch [24,32].

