#### User Experience

Children will provide subjective assessments of the VR MRI app using a 0-100 graphic rating scale at T1. They are asked (1) to rate the amount of “fun” they had during the VR preparation (no fun to most fun); (2) to what extent they felt nausea as a result of experiencing the virtual world (no nausea to severe nausea/vomiting [VR condition only]); (3) how real the objects in the virtual world seemed (“completely fake” to “indistinguishable from a real object” [VR condition only]); and (4) to what extent they felt like they went into the virtual world while experiencing VR (“I did not feel like I went into the virtual world at all” to “I went completely into the virtual world” [VR condition only]). Adherence will also be addressed in the user experience questionnaire by asking children and parents how often and how long they used the VR preparation app.

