#### Secondary Study Parameter(s)

The main secondary outcomes are child preprocedural anxiety at T2 and parental anxiety both before and during the procedure.

For the child’s preprocedural anxiety, we will employ an identical analysis as for the primary end point. For parental anxiety, a repeated measures ANCOVA will be conducted with parental anxiety at T2 and T3 as within variable and group (VR vs CAU) as between variables. The analysis will be corrected for age, sex, baseline anxiety, and CBCL scores as well as type of MRI.

To identify medical or psychosocial moderators for treatment response to VR, we will perform exploratory linear regression analyses with child anxiety at T2 and T3. Predictor variables that will be examined are SES, age, sex, type of MRI, preprocedural child and preprocedural parental anxiety, and child emotional and behavioral problems. The user experience of children in the VR condition will be examined with descriptive analyses.

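### The efficacy models correct for baseline anxiety, but the text describes no anxiety score taken before the VR intervention; if the T2 score fills that role, the primary estimate loses part of the VR effect

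*Protocol article*

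**What the plan says.** Under Primary Study Parameter(s), the protocol article specifies an ANCOVA of the T3 child VAS: "T3; VAS child, continuous score), corrected for age, sex, baseline anxiety, and CBCL scores as well as type of MRI". The anxiety covariate is given neither an instrument nor a time point.

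Under Secondary Study Parameter(s), child anxiety at T2 is a main secondary outcome, for which "we will employ an identical analysis as for the primary end point". Parental anxiety at T2 and T3 is analysed by repeated measures ANCOVA, again corrected for baseline anxiety.

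The measurement schedule under Outcome Measures is explicit:

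- Child STAI-C: "The anxiety level of participants is measured before and after the MRI scan (T2 and T3) with the STAI-C".
- Child VAS: "The participants select the expression that fits their feeling before and after the MRI scan (T2 and T3". The staff VAS is also at T2 and T3.
- Parental STAI: "Parents/guardians rate their own feelings of anxiety with the STAI at T2 and T3".

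Patient Recruitment and Procedure defines the second time point as "T2, the day of the MRI scan, before the procedure will start (in the waiting room". The same section has families randomised after consent, with the VR group then using the app at home. The instruments placed at T1 are the CBCL and the app rating: "Children will provide subjective assessments of the VR MRI app using a 0-100 graphic rating scale at T1".

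**The concern.** A baseline covariate in a randomised comparison should be unaffected by treatment. On the text, the only anxiety score that precedes T3 is the T2 score, and T2 comes after the home intervention. The Introduction hypothesises that VR will lower preprocedural child anxiety, so by the trial's own reasoning T2 anxiety lies between VR and T3 anxiety. Correcting for it would change the question from how much VR preparation lowers anxiety during the scan to how much it does so beyond what it had already achieved in the waiting room. The better VR works before the scan, the smaller the primary estimate becomes.

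The other two models would fare worse. With T2 as the baseline, the T2 analysis would adjust the outcome for itself, and the parental analysis would use one of its two outcome measurements as a covariate.

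**Working it through.** **Which scores could serve as the baseline**

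| Score | Time point in the text | Before VR use? |
|---|---|---|
| Child STAI-C | T2, T3 | No |
| Child, parent and staff VAS of child anxiety | T2, T3 | No |
| Parental STAI | T2, T3 | No |
| CBCL | T1 | Not stated; not an anxiety instrument, and already a separate covariate |
| App rating | T1 | No, since it rates the VR experience |

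No anxiety score is left that precedes the intervention. T1 is a window covering the weeks before the scan. The app rating shows that part of it follows VR use, but not that all of it does.

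**The plan's own figure**

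Sample Size gives d = 0.5, two-sided alpha .05, power .80 and 64 per group. A two-sample t-test needs 63.8, so 64 per group, and has power 0.801 at that size. The stated 128 reproduces.

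**What a T2-adjusted ANCOVA would estimate**

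Let d3 be the VR effect on T3, d2 the VR effect on T2 (both in SD units, as reductions) and r the within-group T2–T3 correlation.

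- Adjusted effect = d3 − r·d2
- Residual SD = √(1 − r²)
- SE = √(1 − r²) × √[(2/64)(1 + d2²/4)]
- Power from the noncentral t with 128 − 3 = 125 df. Only group and the T2 score are modelled; the other covariates are left out for simplicity.

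From the documents: d3 = 0.5 and 64 per arm. Assumed, because the documents give neither: r from 0.3 to 0.7, and d2 from 0 to 0.5.

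Worked case, r = 0.5 and d2 = 0.5: effect 0.5 − 0.5 × 0.5 = 0.25; residual SD √0.75 = 0.866; SE 0.866 × √(0.03125 × 1.0625) = 0.158; ratio 0.25/0.158 = 1.58; power 0.35.

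| d2 | Estimate at r = 0.3 / 0.5 / 0.7 | Power at r = 0.3 / 0.5 / 0.7 |
|---|---|---|
| 0 (true pre-intervention score) | 0.50 / 0.50 / 0.50 | 0.84 / 0.90 / 0.98 |
| 0.10 | 0.47 / 0.45 / 0.43 | 0.79 / 0.83 / 0.92 |
| 0.25 | 0.425 / 0.375 / 0.325 | 0.70 / 0.67 / 0.72 |
| 0.50 | 0.35 / 0.25 / 0.15 | 0.52 / 0.35 / 0.21 |

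Simulation with 4,000 trials per case agrees: estimate 0.252 and power 0.36 at r = 0.5, d2 = 0.5; 0.149 and 0.20 at r = 0.7, d2 = 0.5; 0.377 and 0.67 at r = 0.5, d2 = 0.25.

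At d2 = 0.10 power can exceed the unadjusted 0.80, because the covariate also removes residual variance. The estimate still falls short of the total effect. It is intact only if VR does not change T2 anxiety or if T2 and T3 are uncorrelated.

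**The case against.** A reader might infer that the planned primary analysis does adjust for a mediator. The documents do not support that as a statement of fact. No section equates baseline anxiety with T2. Secondary Study Parameter(s) points the other way: adjusting T2 for itself, or the parental T2 and T3 scores for T2, makes so little sense that the authors may have had another score in mind. The same section calls the waiting-room measure preprocedural anxiety when it lists moderators, which is a different term. Figure 2, which sets out the instruments at each time point, is not shown and may list an anxiety score at T1. The full protocol or analysis plan may define the covariate.

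Trait anxiety is another candidate, since the article says that the STAI-C and STAI measure trait as well as state. A trait score should move less under VR than a state score. The text nevertheless times these instruments at T2 and T3, so it too would be a post-allocation score.

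The size is also open to challenge. Neither d2 nor r is documented, and the larger losses assume that VR lowers T2 as much as T3. With a small T2 effect the loss is small.

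These points make the finding conditional. They do not remove it, because the covariate list and the described measurement schedule do not fit together. If Figure 2 does show an earlier score, the Child Anxiety and Parental Anxiety sections must be reconciled with it, and the score must be shown to precede VR use.

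**Conclusion.** The concern holds in conditional form. The article corrects its efficacy models for a covariate that its text never describes as being measured before the intervention, and the scores it does describe are unsuitable for that role. If T2 is used, the T3 model estimates d3 − r·d2 instead of the total effect. With d3 = 0.5 and 64 per arm, and with r of 0.3 to 0.7 and d2 of 0.1 to 0.5 assumed, the estimate lies between 0.47 and 0.15 SD and power between 0.92 and 0.21, against 0.80 unadjusted. The documents do not fix a single figure in that range. The sample size calculation is not in error. The matter should be settled before the data are analysed, since it determines what the primary estimate means.

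**What to change.** State in the analysis section that no anxiety score from T2 or later enters any efficacy model as a covariate. Retain baseline anxiety only if it is a named score, with a stated time point, obtained before allocation or before the VR log-in code was issued. Otherwise drop it and keep age, sex and type of MRI. Apply the same rule to the T2 model and the parental model. If an earlier score exists, bring the Child Anxiety and Parental Anxiety sections into line with Figure 2.

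Keep the CBCL as a covariate in its own right, not as a substitute for baseline anxiety: the article describes it as a measure of behavioural and emotional problems. Confirm that it is completed before allocation or VR use. It is collected at T1, a window that also contains the app rating, so it cannot be taken for granted that it was fixed before randomisation, although its six-month recall makes a VR effect unlikely.

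The cost is a change of wording and no new data. If no pre-intervention score exists, the model gives up some precision; for comparison, a true pre-intervention score would give power of 0.84 to 0.98 for r of 0.3 to 0.7, against 0.80 without adjustment.

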## Methods

### VR Design

The VR tool encompasses a highly realistic virtual environment that replicates the MRI experience of the Erasmus University Medical Center (MC)–Sophia Children’s Hospital, Rotterdam, the Netherlands. The designed virtual MRI environment does not significantly differ from that of the Amsterdam University Medical Centers (UMC).

A multidisciplinary team, consisting of child-life specialists, child psychologists, a child psychiatrist, anesthesiologists, a 3D-acting director, and a 3D project manager designed the script of the VR experience. Working together with specialized VR developers and animators, multiple 3D characters, asset, and environment artists created the scenery and character modeling. During the design and development phases, team meetings were held to review the process and make any necessary adjustments. Overall, the main goal was to create a dynamic and interactive environment that will prepare children for the MRI procedure in a realistic and child-friendly manner. Once the VR software was created, it was pilot-tested in healthy children (n=10). Based on the observations and responses of the pilot test, final adjustments were made.

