### Study Design

This multicenter, single-blinded, RCT is being performed at the Erasmus MC–Sophia by the Departments of Child and Adolescent Psychiatry/Psychology, Radiology, and Pediatric Anesthesiology and at the Amsterdam UMC–Emma Children’s Hospital by the Department of Radiology. Children (N=128) will be randomly allocated to 2 parallel groups: VR smartphone application (n=64) or CAU (n=64). CAU involves an information letter given to the parents that consists of information about the MRI examination, the screening questionnaire that is used, and how to best explain the MRI exam to their child. Randomization will be performed as block randomization with a 1:1 allocation.

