### Inclusion and Exclusion Criteria

Eligible participants are children aged between 6 and 14 years undergoing an MRI scan at the Erasmus MC–Sophia Children’s Hospital or the Amsterdam UMC–Emma Children’s Hospital (2 specialized children’s university hospitals in the Netherlands) in the period between May 2021 and December 2022. Children that meet the following criteria will be excluded from participating: any intellectual disability, inability of parents to read or write in the Dutch language, epilepsy, visual impairments, and the need of general anesthesia during the scan.

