### Sample Size

To conduct analysis of covariance (ANCOVA) on the level of periprocedural anxiety at time point (T) 3 (primary outcome) with a Cohen *d* of 0.5, an α of .05 (2-tailed), and a power of .80, a sample size of 128 patients is needed (64 patients per group). Based on earlier studies, we anticipate finding a medium effect size [16].

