### Randomization

Participants will be randomly allocated to the intervention (VR) or control group (CAU) with a 1:1 allocation. A computer-generated randomization schedule will be used, stratified by age group (aged 6-10 vs 10-14 years) and the type of MRI (upper body vs lower body).

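### Hospital is in neither the randomisation strata nor the ANCOVA covariates of this two-hospital trial; the cost is a modest loss of precision that a one-degree-of-freedom term would recover

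*Protocol article*

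**What the plan says.** The protocol article describes a trial at two sites. Study Design states: "This multicenter, single-blinded, RCT is being performed at the Erasmus MC", and goes on to name the Amsterdam hospital. Inclusion and Exclusion Criteria calls the sites "2 specialized children’s university hospitals in the Netherlands".

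Hospital could be handled in several places and is named in none of them:

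- **Randomization:** the schedule is "stratified by age group (aged 6-10 vs 10-14 years) and the type of MRI (upper body vs lower body".
- **Patient Recruitment and Procedure:** this second description of the stratification names only the type of scan.
- **Study Design:** "Randomization will be performed as block randomization with a 1:1 allocation", with no statement that blocks are formed within hospital.
- **Primary Study Parameter(s):** the child-rated VAS at T3 is compared by ANCOVA, "corrected for age, sex, baseline anxiety, and CBCL scores as well as type of MRI". If the data are not normal, a Mann-Whitney test is used instead, and that test takes no covariates.
- **Secondary Study Parameter(s):** child anxiety before the scan is analysed in the same way as the primary outcome. The repeated measures model for parental anxiety uses the same covariates. The exploratory moderators do not include hospital either.

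**The concern.** The outcome is a child's anxiety in the scanner, and the setting and staff of each hospital may plausibly influence it. The Introduction itself treats the scanner environment as a source of anxiety. The plan adjusts for the type of MRI but not for the hospital where the MRI is done.

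If mean anxiety differs between the hospitals, the difference adds to the residual variance. If the arms happen to be unevenly spread over the hospitals, nothing in the analysis corrects for it. What is at stake is some of the power and precision of the primary comparison.

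This is not a detail left open for a later analysis plan. The article prints specific lists of strata and covariates, and hospital is on neither.

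**Working it through.** **Inputs from the protocol article (Sample Size, Study Design).** "an α of .05 (2-tailed), and a power of .80, a sample size of 128 patients is needed (64 patients per group"; 1:1 allocation; two hospitals; planned standardised difference d = 0.5.

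**Assumed, because the article does not give them.** D is the difference in mean anxiety between hospitals that remains after the other covariates, in within-hospital SD units; values of 0.2 to 0.8 are tried. p is the share of children from one hospital; 50:50 is the main case and 80:20 the alternative. The planned d of 0.5 is read on the within-hospital SD.

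**Step 1: the stated sample size.** The normal approximation gives n = 2(1.960 + 0.842)² / 0.5² = 62.8, so 63 per arm and 126 in total. The exact two-sample t calculation gives 64 per arm, 128 in total, with power 0.801. The stated figure is reproduced.

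**Step 2: cost of the extra term.** One fewer residual degree of freedom at 64 per arm leaves power at 0.801; the loss is below 0.001.

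**Step 3: cost of leaving hospital out.** Residual variance becomes 1 + p(1−p)D², the effective d becomes 0.5/√(1 + p(1−p)D²), and the N needed to match 128 with the term is 128(1 + p(1−p)D²), rounded up.

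**Step 4: chance imbalance.** Suppose each hospital contributes 64 children and 64 of the 128 go to VR. The number of VR children from one hospital then has hypergeometric variance 64 × 0.5 × 0.5 × 64/127 = 8.06, SD 2.84. The difference between arms in hospital share has SD 2 × 2.84/64 = 0.089, and a 95% range of ±1.96 × 0.089, about ±17 percentage points. The shift in the estimate is that range times D.

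Results at 50:50:

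| D | p(1−p)D² | Share of variance | Effective d | Power without hospital | Power with hospital | N to match 128 | 95% chance shift (SD) |
|---|---|---|---|---|---|---|---|
| 0.2 | 0.0100 | 1.0% | 0.498 | 0.798 | 0.801 | 130 | ±0.035 |
| 0.3 | 0.0225 | 2.2% | 0.494 | 0.793 | 0.801 | 131 | ±0.052 |
| 0.5 | 0.0625 | 5.9% | 0.485 | 0.777 | 0.801 | 136 | ±0.087 |
| 0.8 | 0.1600 | 13.8% | 0.464 | 0.741 | 0.801 | 149 | ±0.139 |

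At 80:20 the power without hospital is 0.799, 0.796, 0.786 and 0.762 for the same four values of D. The imbalance range is ±14 percentage points.

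If d = 0.5 is read on the total SD instead, power without hospital is 0.801, and the term raises it at 50:50 to 0.810 (D = 0.3) or 0.825 (D = 0.5). The gain is of similar size on either reading.

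**Step 5: one loss, not two.** At D = 0.5 the chance shift has variance (0.089 × 0.5)² ≈ 0.0020. The extra residual variance adds 2 × 0.0625/64 ≈ 0.0020 to the variance of the estimate. These are the same quantity, so the standard error already reflects the imbalance.

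**Step 6: type I error.** In simulations of 20,000 trials per setting (50:50, neither stratified nor adjusted), the rejection rate under no effect was 0.049, 0.052 and 0.050 for D = 0.3, 0.5 and 0.8. Simulated power at d = 0.5 was 0.793, 0.772 and 0.744, close to the table.

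**The case against.** **The hospital difference is assumed.** The article reports none. Both sites are specialised children's university hospitals in one country, and the existing covariates would absorb part of any difference in case mix. This stands: only what remains after those covariates counts, and values of 0.5 SD or more may be generous.

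**The full protocol may use a randomisation list per hospital.** The article is condensed and cannot rule this out, but its own descriptions of the strata omit hospital. Separate lists would also not make the term unnecessary. With balance by hospital but no term in the model, simulated type I error fell to 0.046 at D = 0.5 and 0.035 at D = 0.8, and simulated power stayed below the adjusted analysis (0.782 against 0.802, and 0.757 against 0.800).

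**Stronger readings that the article does not support:**

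- *The VR scene fits only one hospital.* VR Design says the scene "replicates the MRI experience of the Erasmus University Medical Center" and its Sophia Children's Hospital. The next sentence, however, says that the virtual environment is not significantly different from the one in Amsterdam, and Strengths and Limitations presents the app as usable at any hospital as it is. A better fit at one site would in any case be a treatment-by-hospital interaction. It would not be noise between hospitals, and a hospital main effect would not remove it.
- *Chance imbalance biases the result.* Steps 5 and 6 show that it does not, over randomisations.
- *Different staff raters at each site distort the primary outcome.* Primary Study Parameter(s) uses the child's own VAS; the staff VAS is a separate measure.

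**Conclusion.** The omission is real and specific: hospital is in no stratum and no model that the article lists. The consequence is a loss of precision that is probably small. With a 50:50 split, power at N = 128 falls by less than 1 percentage point for a remaining hospital difference of up to 0.3 SD, and by about 2 points at 0.5 SD. It falls by about 6 points only at 0.8 SD, and nothing in the article indicates a difference that large. The sample size of 128 is correct for its stated inputs. These sizes rest on an assumed hospital difference and split, so they are a range and not an estimate. The change is worth making because it costs almost nothing.

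**What to change.** Before the outcome data are analysed by arm, add hospital (two levels) as a fixed factor to the primary ANCOVA, to the matching model for child anxiety before the scan, and as a between-subject factor to the repeated measures model for parental anxiety. Recruitment was already under way when the article appeared, so the analysis model is the practical place for the change.

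Carry hospital into the nonnormality path as well. The plain Mann-Whitney test would drop the term, so replace it with, for example, a rank test stratified by hospital (van Elteren).

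Optionally, report the VR minus CAU difference by hospital, descriptively. This would check the article's statement that the scene suits both sites; it does not respond to a demonstrated problem.

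The cost is 1 degree of freedom, less than 0.001 in power, and no new data, since the hospital of every child is known.

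### The primary test depends on an undefined normality check of a six-face ordinal score, and the fallback Mann-Whitney test drops every planned covariate

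*Protocol article*

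**What the plan says.** All references are to the protocol article.

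- **Child Anxiety** describes the instrument: "The VAS shows 6 faces in order from not scared at all (most left face) to extremely scared". The response is a choice of one face: "The participants select the expression that fits their feeling before and after the MRI scan (T2 and T3"). The score can take at most six values.
- **Primary Study Parameter(s)** gives the main analysis, "we will compare the VR group to the CAU group with an ANCOVA", and defines the T3 outcome and its adjustment as "VAS child, continuous score), corrected for age, sex, baseline anxiety, and CBCL scores as well as type of MRI". The next sentence is the exception: "In case of nonnormality, we will perform a Mann-Whitney" U test.
- **Secondary Study Parameter(s)** gives child anxiety at T2 the same analysis, so the exception applies there too.
- **Randomization** stratifies by age group and type of MRI.
- **Sample Size** begins "To conduct analysis of covariance (ANCOVA) on the level of periprocedural anxiety" and assumes an effect "with a Cohen *d* of 0.5", two-sided α of .05 and power .80, arriving at 64 per group.
- **Overview** (Statistical Analysis) says that "multiple imputation will be used to control for bias due to missing data".

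**The concern.** A six-category item cannot be normally distributed, so a condition of nonnormality invites the switch from the start. The condition is also undefined. Two analysts with the same data could follow the text faithfully and report different primary tests, one on the raw score and one on residuals.

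The two tests do not answer the same question. ANCOVA estimates an adjusted mean difference with a confidence interval. The Mann-Whitney test compares ranks and takes no covariates, so type of MRI, CBCL scores, sex, age and baseline anxiety all leave the primary analysis. Age and type of MRI are the stratification factors. The fallback also fits less easily with the planned multiple imputation, because its usual output is a test statistic and p-value, not an estimate with a standard error.

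At stake are a primary analysis that the plan does not determine in advance and the loss of whatever precision the covariates would bring.

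**Working it through.** **1. The stated sample size.** Inputs from Sample Size: d = 0.5, two-sided α = 0.05, power 0.80.

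Normal approximation: n per arm = 2(z₀.₉₇₅ + z₀.₈₀)² / d² = 2(1.960 + 0.842)² / 0.25 = 62.8, so 63. The exact two-sample t calculation gives 63.77, so 64 per arm and 128 in total, with power 0.801. The figure reproduces. It is the size of an unadjusted comparison and takes no credit for covariates (R² = 0).

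**2. What the fallback keeps.** With normal data the Mann-Whitney test has relative efficiency 0.955. Then 64 × 0.955 = 61.1 effective patients per arm, 0.5 × √(61.1/2) = 2.76, and power is Φ(2.76 − 1.96) = Φ(0.80), about 0.79.

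**3. How often the switch would be made.** Assumptions, because the documents give none of these: a latent normal variable cut into six categories, five score distributions, latent covariate R² of 0, 0.3 or 0.5, latent d of 0 or 0.5, 64 per arm, 2000 runs per cell, Shapiro-Wilk at 5%.

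| Score distribution | Rejects, raw score | Rejects, ANCOVA residuals |
|---|---|---|
| Floor-heavy | 100% | about 82–100% |
| Moderate skew | 100% | 43–100% |
| Mild skew | 100% | 19–100% |
| Uniform | 100% | 9–100% |
| Near-symmetric | 100% | 3–80% |

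The residual rate falls as R² rises. An informal rule, absolute skewness above 1, triggered in 0–99% of runs.

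**4. What the switch costs.** Same model, latent d = 0.5 (observed d about 0.43–0.49); power of ANCOVA against Mann-Whitney:

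| Latent R² | ANCOVA | Mann-Whitney | Examples of the loss |
|---|---|---|---|
| 0 | 0.67–0.77 | 0.69–0.76 | mild skew: 0.744 − 0.742 = 0.002 |
| 0.3 | 0.78–0.89 | 0.67–0.76 | mild skew: 0.868 − 0.744 = 0.124 |
| 0.5 | 0.86–0.96 | 0.69–0.75 | floor-heavy: 0.861 − 0.690 = 0.171; near-symmetric: 0.960 − 0.748 = 0.212 |

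A separate run put half the controls at the lowest face, with observed d about 0.49 and robust (HC3) standard errors. It gave 0.82 against 0.81 at R² 10%, 0.85 against 0.81 at 20% and 0.87 against 0.79 at 30%: losses of 1, 4 and 8 points. Over all the runs the loss is none to about 5 points at R² of 0–0.1, about 7–14 at 0.3 and about 12–21 at 0.5.

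**5. Validity.** With no effect, ANCOVA rejected in 0.042–0.056 of runs. The two-stage rule (test residuals, then choose) rejected in 0.041–0.056. Nonnormality of this score gives no validity reason to leave ANCOVA at 64 per arm, and the switch does not inflate type I error.

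**The case against.** The strongest reply is that little is lost. ANCOVA assumes normal residuals, not a normal outcome, and how normality is judged is often left to an analysis plan. If residuals are meant, the switch may be rare. The trial was sized as an unadjusted comparison, so the fallback roughly keeps its planned power. If the covariates explain about 10% of the variance, the loss is a few points at most. Much of this stands, and it rules out several stronger readings that a reader might infer:

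- *The switch is virtually certain.* This holds only if the six-level score itself is formally tested. The sentence follows the outcome definition, so that is a natural reading, but the text does not say it.
- *Scores will pile up at the lowest face.* The Introduction cites one study in which about half of children had anxiety and discomfort. That is not a distribution of face scores, and the article gives none.
- *The test cannot be combined with multiple imputation.* It can, through the probability index P(X<Y) + 0.5 P(X=Y) and its standard error. This is less usual, not impossible.
- *The trial would be underpowered, or would not run the analysis it was sized for.* The first two working steps do not support this.

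The reply does not rescue the rule. A low trigger rate under one unstated reading and a rate of 100% under another confirm that the plan does not determine its primary analysis. The article states the switch itself, so this is not merely detail left to an unseen document.

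**Conclusion.** The point holds as a defect that should be fixed, not one that threatens the trial's validity. A six-level ordinal score is labelled continuous, and an undefined look at the data decides between an adjusted mean difference and an unadjusted rank comparison, at T3 and again at T2. Error control and the nominal 80% power are essentially intact; the cost is the precision gain set out above.

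The size of that cost rests on assumed score distributions, an assumed R² and Shapiro-Wilk as the check. The upper figures need strongly prognostic covariates. Baseline anxiety is the obvious candidate, but the readable text places child anxiety only at T2 and T3, and T2 comes after VR use at home. Figure 2 is not shown, so a T1 measure cannot be excluded. Without one, the smaller losses are the more plausible.

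**What to change.** 1. Delete the normality switch for both T3 and T2.
2. Make the covariate-adjusted ANCOVA the single primary analysis, with heteroscedasticity-robust (for example HC3) standard errors. Report the adjusted mean difference with its 95% CI, pooled over imputations by Rubin's rules.
3. Use only covariates measured before randomisation, and name the baseline anxiety measure. The T2 score must not serve as baseline: it follows home VR use, and in the T2 analysis it is the outcome itself. If no earlier child anxiety score exists, leave that covariate out. User Experience places ratings of the app at T1, so the plan should also state that T1 covariates are collected before allocation.
4. Describe the face score as ordinal with six levels.
5. Use a proportional-odds model with the same covariates, or the Mann-Whitney test, only as a sensitivity analysis.

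The cost is a change of wording and slightly more analysis work; the sample size stands. The drawback is that the headline result is a mean difference on an ordinal score, which the proportional-odds sensitivity analysis helps to put in context.
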